### Economic evaluation

We will perform an economic evaluation from the societal and health provider perspectives that include all relevant costs and outcomes. A cost-effectiveness analysis as well as a cost-utility analysis will be conducted following guidelines from the International Society for Pharmacoeconomics and Outcomes Research (ISPOR) Good Research Practices Task Force Report and the recommendations of the Consolidated Health Economic Evaluation Reporting Standard (CHEERS) [92, 93]. In the cost-effectiveness analyses, symptom-free status via SPS and SIAS will be used as clinical outcome. For cost-utility analyses, quality-adjusted life years (QALYs) will be calculated based on the AQOL-8D. EQ-5D-5L will be used only in sensitivity analyses. We will compare both groups in terms of incremental costs and incremental effects, by calculating the incremental cost-effectiveness ratio (ICER). We will use bootstrapping (*N* = 5000) and 95% confidence intervals in percentiles to test the robustness of the ICER and to quantify the uncertainty surrounding the ratios. The results will be shown in a cost-effectiveness plane and in a cost-effective acceptability curve. Additionally, the robustness of the base-case findings will be tested with a multi-way sensitivity analysis (i.e. ± 50% intervention costs, costs outliers, EQ-5D-5L as alternative instrument to calculate QALYs).

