### Measurements

A detailed overview of all measures at baseline (t0), 10-week post-treatment (t1) and 6-month follow-up is given in Table 2.

**Table 2 Tab2:** Measurements and time of assessment

Instrument	Abbreviation	Aim	Time of assessment		
			t0	t1	t2
Clinician administered					
Structured Clinical Interview for DSM-IV Axis I Disorders	SCID-I	DSM-IV Axis I disorders	✔		✔
Self-report ratings					
Primary Outcome Measure					
Social Phobia Scale^a^	SPS	Symptoms of SAD	✔	✔	✔
Social Interaction Anxiety Scale^a^	SIAS	Symptoms of SAD	✔	✔	✔
Secondary Outcome Measure					
Liebowitz Social Anxiety Scale	LSAS-SR	Social anxiety symptoms	✔	✔	✔
Beck Depression Inventory II	BDI-II	Symptoms of depression	✔	✔	✔
Brief Symptom Inventory	BSI	Psychiatric symptoms	✔	✔	✔
Inventory of Interpersonal Problems	IIP-64	Interpersonal problems	✔	✔	✔
Fear of Positive Evaluation Scale	FPES	Fear of positive evaluation	✔	✔	✔
Disqualification of Positive Social Outcomes Scale	DPSOS	Fear of positive evaluation	✔	✔	✔
EuroQol (EQ-5D-5 L)	EQ-5D-5 L	Quality of life	✔	✔	✔
Assessment of Quality of Life (AQol)	AQoL-8D	Quality of life	✔	✔	✔
Client Satisfaction Questionnaire	CSQ-8	Client satisfaction			
Trimbos/iMTA Questionnaire for Costs associated with Psychiatric Illness	TiC-P	Cost-effectiveness	✔		✔
Credibility Expectancy Questionnaire	CEQ	Treatment expectancy			

t0 Baseline; t1 10 weeks; t2 6 months; Assessments ✔ = intervention and control group;  = intervention group ^a^ process measures assessed every 2 weeks

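### The percentile confidence interval planned for the ICER carries no condition on where the bootstrap replicates fall, and can be misread if a non-negligible share shows a negative QALY difference

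*Protocol article*

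**What the plan says.** Under Economic evaluation, the protocol article plans a cost-effectiveness analysis with symptom-free status as the effect, and a cost-utility analysis in which "quality-adjusted life years (QALYs) will be calculated based on the AQOL-8D". On the comparison it says: "We will compare both groups in terms of incremental costs and incremental effects", summarised as an ICER. Uncertainty comes from 5000 bootstrap replicates and "95% confidence intervals in percentiles to test the robustness of the ICER and to quantify the uncertainty surrounding the ratios". The interval is thus placed on the ratio itself, and the text does not say what happens when replicates fall in more than one quadrant. The section adds: "The results will be shown in a cost-effectiveness plane and in a cost-effective acceptability curve".

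The horizon is six months after randomisation (Procedure), with 100 participants per arm (Participants). The intervention cost is EUR 178.50 including VAT (Cost measures).

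**The concern.** A ratio of differences loses information about sign. A negative ICER arises when the intervention is cheaper and better (south-east, dominant) and also when it is dearer and worse (north-west, dominated). A positive ICER arises when it is dearer and better (north-east) and also when it is cheaper and worse (south-west), where the decision rule runs the other way. Sorting the replicated ratios and cutting at the 2.5th and 97.5th percentiles ignores these differences.

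The condition that matters is the sign of the effect difference. If all effect differences are positive, a lower ratio does mean better value in the sense needed here: a negative ratio can only be dominant. Once a material share of effect differences is negative, dominated replicates are placed at the low end of the list, next to dominant ones. The reported lower limit may then be negative because some replicates were harmful and costly, while a reader takes it as evidence of possible savings. Cost-effectiveness is a stated aim of the trial and is meant to inform policy makers, so this number would be read.

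**Working it through.** **The plan's own figure.** The economic section states no expected ICER, variance or interval to reproduce. The intervention cost does reproduce: 150 × 1.19 = EUR 178.50.

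**Inputs from the article.** n = 100 per arm; horizon six months; EUR 178.50 is used as the mean cost difference, which itself assumes no change in other costs.

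**Assumptions (none is in the article).** QALY gain dE = 0.01 to 0.02; QALY SD 0.05 to 0.08 per person; cost SD EUR 500 to 4,000 per person; correlation of cost and effect differences −0.1; normal bootstrap cloud.

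**Step 1: standard errors.** SE = SD × √(2/100). For QALY SD 0.08: 0.08 × 0.1414 = 0.0113. For cost SD 500: 500 × 0.1414 = EUR 70.7.

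**Step 2: share of replicates with a negative effect,** Φ(−dE/SE), for QALY SD 0.08.
- dE = 0.02: Φ(−1.77) = 3.9%
- dE = 0.01: Φ(−0.88) = 18.8%

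**Step 3: share with a negative cost difference,** Φ(−178.50/SE).
- SD 500: 0.6%
- SD 1,000: 10%
- SD 2,000: 26%
- SD 4,000: 38%

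This spread alone moves replicates from north-east to south-east, which does not break the ordering.

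**Step 4: a case where the interval misleads.** dE 0.02 (SD 0.08), cost SD 500. The point ICER is 178.50/0.02 = EUR 8,925 per QALY. By simulation about 96% of replicates are north-east, 3.8% north-west and 0.6% south-east. The percentile interval is about −36,000 to +71,000. Of the negative ratios, 3.8/(3.8 + 0.6), about 86%, are dominated. Ordering the same replicates by their angle on the plane, which respects the quadrants, gives a lower limit near +1,600 and an upper end inside the dominated quadrant. The percentile interval therefore suggests possible savings at the lower end and hides possible domination at the upper end.

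**Step 5: a case with more spread.** dE 0.02 (SD 0.08), cost SD 2,000: about 70% north-east, 26% south-east, 3% north-west and 1% south-west; percentile interval about −60,000 to +112,000.

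**Step 6: a case where the interval is usable.** dE 0.02 (SD 0.05), cost SD 1,000: 89% north-east, 10% south-east, 0.2% north-west and under 0.1% south-west. The percentile limits are about −5,300 to +41,300; ordering by angle gives about −5,000 to +43,000. The two agree closely.

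**Step 7: net monetary benefit in the Step 4 case,** at an illustrative λ = EUR 20,000 per QALY.
- Mean = λ·dE − dC = 400 − 178.50 = EUR 221.50
- Variance = λ²·SE_E² + SE_C² − 2λ·ρ·SE_E·SE_C = 51,200 + 5,000 + 3,200 = 59,400, so SE = 243.7
- 95% interval = 221.50 ± 1.96 × 243.7, about −256 to +699

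This interval has a single direction: higher is always better value.

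**The case against.** The strongest reply has three parts.

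First, spread over quadrants is not in itself the fault. When effects are nearly all positive, the ratio interval is ordered and readable, as Step 6 shows. The low intervention cost argues only for spread between north-east and south-east. This stands. A reader might infer that an ICER percentile interval is meaningless in this trial, or that the failure is almost certain; the article gives no variances from which either could be shown.

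Second, the problem is less likely for the cost-effectiveness analysis on symptom-free status. With assumed rates of 15% against 30%, SE = √(0.15·0.85/100 + 0.30·0.70/100) = 0.058, and Φ(−0.15/0.058) = 0.5% of replicates have a negative effect. For 20% against 35% the figure is 0.8%, and for 10% against 20% it is 2.3%. This also stands, so the point bears mainly on the QALY analysis.

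Third, the plane shows the quadrant split, and the acceptability curve uses the replicates correctly. This limits the harm. It does not correct the interval, to which the article assigns the task of quantifying uncertainty and which would be reported beside the ICER.

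A reader might also infer that costs and QALYs will be compared without their baseline values, since the economic section mentions no covariates. The article does not say so. That section neither includes nor excludes adjustment, the Analysis section plans ANCOVA with baseline scores for continuous outcomes, and an article may leave such detail to a fuller plan. It is no finding.

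**Conclusion.** The concern holds in a conditional form. The article fixes a percentile interval on the ICER without any condition on the sign of the effect difference. For six-month QALYs with 100 per arm, a negative-effect share of about 4% to 19% is plausible under an assumed gain of 0.01 to 0.02 and an assumed QALY SD of 0.08. In that range the limits can mislead, as Step 4 shows. With a smaller QALY SD, or for symptom-free status at the rates assumed above, the share may be negligible and the interval acceptable. The quadrant shares and interval limits rest on assumed effects, SDs and correlation; only the sample size, the horizon and the intervention cost come from the article. The primary efficacy analysis is not affected. The change is worth making because the alternative is readable in every case and costs almost nothing.

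**What to change.** In Economic evaluation, replace the percentile interval of the ICER as the measure of uncertainty with the incremental net monetary benefit and its bootstrap 95% interval at willingness-to-pay values stated in advance. State such values separately for a QALY and for a symptom-free case. Keep the ICER as a point estimate, together with the planned plane and acceptability curve, and report the percentage of replicates in each quadrant. Give a percentile interval for the ICER only if replicates with a negative effect difference are negligible, by a threshold fixed beforehand.

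The same 5000 replicates serve for all of this. The cost is the choice of willingness-to-pay values, a few lines of wording and minor programming; no new data are needed.

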## Discussion

SAD is a highly prevalent mental health disorder, also among university students. Affected students suffer from lower quality of life, high burden of psychological strain and reduced academic functioning. Internet-based interventions represent a low-threshold, easily accessible, and flexible treatment which may help to overcome the low utilization rates of those in need.

Within this study we intend to extend the evidence of internet-based self-help for SAD regarding efficacy and cost-effectiveness. Particularly, we want to strengthen the evidence of unguided treatments, since the question how much support is needed remains unanswered given prior mixed results. On the one hand, results from two meta-analyses [94, 95] found self-help programs with support to be more effective and with lower attrition rates compared to no support. Whereas a recent meta-analysis on internet-based guided cognitive behavioral interventions for anxiety disorders in general did not find such differences, indicating that effects between current guided and unguided treatments for anxiety might be smaller than previously anticipated [25].

There may be several other factors such as the intensity of screening procedures [52], the length, structure and comprehensiveness of the self-help program itself [96], the extent of support needed depending on the disorder [95] as well as human substitutes such as automated reminders [97], which systematically confound whether guided interventions lead to superior results compared to unguided interventions [98].

This study will have three noteworthy limitations. First, if this study demonstrates clinically relevant effects for unguided self-help for SAD, it has to be taken into account that this evidence will be based on an RCT, which is characterized by a highly structured participation and research attention. This is usually not the case when self-help interventions are offered in routine care. Since the securing of commitment represents an adherence-promoting element in self-help interventions, it has been argued that effect sizes of pure self-guided interventions found in RCTs are significantly overestimated for what can be expected in routine care [99], when no additional measures to increase adherence are applied. Hence, in order to achieve similar effects outside laboratory conditions, a clear concept for ensuring adherence through minimal guidance from a professional or lay health worker seems favorable.

Second, we will employ an open recruitment strategy in the general student population. Such a procedure mimics a public health approach of student mental health treatment barriers of face-to-face treatment pathways. However, results need to be interpreted cautiously in such a context and may not generalize to classical routine face-to-face clinical practice pathways. A previous study has found that patients undergoing internet-based treatment resembled national general samples more closely than samples from routine face-to-face mental health care [100].

Third, the cost assessment is based on a self-report instrument and it may be argued that self-report data are potentially less accurate compared to data collected directly from public registers. However, comparative studies of self-report questionnaires and diaries have found an acceptable comparability [101]. The remaining risk, however, is likely to be equal across treatments, making it unlikely that it will result in a bias between groups.

## Conclusion

To the best of our knowledge, this study will have the largest unguided RCT intervention group recruited for SAD treatment so far [15, 102]. This study will contribute to the evidence for the efficacy, cost-effectiveness and moderators of unguided internet-based self-help for social phobia in university students. If successful, this intervention would facilitate the adequate allocation of scarce resources and will provide valuable information of a public health approach of SAD treatment. When implemented on large scale, such interventions might help to reduce the immense burden associated with SAD in university students.

## Abbreviations

ANCOVA: Analysis of covariance
AQol: Assessment of Quality of Life
BAföG: German Federal Law on Support in Education
BDI-II: Beck Depression Inventory II
BSI: Brief Symptom inventory
CBT: Cognitive behavioral therapy
CEQ: Credibility expectancy questionnaire
CHEERS: Consolidated Health Economic Evaluation Reporting Standard
CSQ-8: German Client satisfaction questionnaire
DPSO: Disqualification of positive social outcomes
DRKS: German Clinical Trials Register
ECTS: European Credit Transfer System
EQ-5D-5L: European Quality of Life 5 Dimensions 3 Level instrument
FNE: Fear of negative
FPE: Fear of positive evaluation
ICER: Cost-effectiveness ratio
IG: Intervention group
IIP-64: Inventory of Interpersonal Problems
IMI: Internet- and mobile-based self-help intervention
ISPOR: International Society for Pharmacoeconomics and Outcomes Research
LSAS: Liebowitz Social Anxiety Scale
QALYs: Quality-adjusted life years
RCT: Randomized controlled trial
SAD: Social anxiety disorder
SCID: Structured Clinical Interview for DSM Disorders
SIAS: Social Interaction Anxiety Scale
SPS: Social Phobia Scale
TIC-P: The Trimbos and iMTA Treatment Inventory of Costs in Patients with psychiatric disorders (TIC-P)
VAS: Visual analogue scale
WHO: World Health Organization
WLC: Wait-list control group
WMH-ICS: WHO World Mental Health International College Student Initiative
